The factor structure of EWQ as reported by parents and teacher, respectively, prior to the parent-teacher conference and as reported DBED concluded concern from the parent-teacher conference, primarily at baseline, but also at the following half-year registrations for comparative reasons.Agreement between (i) reported concern and DBED concluded concern, respectively, measured by total EWQ score and EWQ sub-scores, and (ii) mental health measured by SDQ Total difficulties score, each sub-scale score, and two SDQ impact scores, respectively, at baseline.Agreement between parent’s and teacher’s mental health report measured by agreement between parent and teacher SDQ scores and the above mentioned SDQ impact scores at baseline and after 12, 24, and 36 months, respectively.Agreement between parents and teacher in possible concerns for the child measured by percentage of EWQ items rated as the three different response options, respectively (satisfied; a bit uncertain; concerned), at baseline and after 12, 24, and 36 months, respectively).Change from reported to concluded concern during the parent-teacher conference measured similarly as the preceding outcome.Satisfaction with the DBED after all parent-teacher conferences measured by the study-specific satisfaction questionnaires for parents and teachers, respectively.Predictors of mental health change during the 5-year follow-up. Mental health is measured by SDQ-scores (Total difficulties score, sub-scales and impact scores) and the predictors (at baseline) are measured by:◦ Parent’s educational level◦ Satisfaction with economic situation◦ Social support◦ Single parenting◦ Close relatives in the vicinity◦ Norwegian language at home?◦ Is Norway parent’s country of origin?◦ Major illness or handicap◦ Level of parental concern◦ Level of teacher concern◦ Level of DBED concluded concern◦ Parent-teacher agreement after the parent-teacher conversation at baseline◦ Level of parental stressPredictors of parental and teacher concern, respectively. Concern is measured by parent and teacher EWQ total score at baseline and changes throughout the 3-year follow-up period in kindergarten, and the predictors are the same as for mental health change.Predictors of parental stress. Parental stress is measured at baseline and changes throughout the total follow-up period of 5 years, and the predictors are the same as for mental health change (except parental stress).Predictors of parent satisfaction. Parent satisfaction is measured by the study-specific satisfaction questionnaire at baseline and changes throughout the 3-year follow-up period in kindergarten, and the predictors are the same as for mental health change.

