## Statistical methods

### Statistical methods for primary and secondary outcomes {20a}

Primary outcome:◦ Possible differences between children in intervention and control kindergartens in mental health trajectories will be estimated by Latent growth curve (LGC) models (gives equal results as linear mixed/multilevel models, given similar parameter specification). Both random intercept fixed slope and random intercept random slope will be analyzed, meaning models with no variance in change (slope) and models with individual differences in slope (random effects). Then the full unstructured matrix with random intercept, random slope, and the covariance between intercept and slope will be tested. Initially, linear change over time will be tested. If not supported with data, different non-linear change models will be explored (quadratic, cubic, piecewise growth). Then, substantial predictors will be entered into the model and analyzed. Also, within level residual structures will be tested.Secondary outcomes:◦ Possible differences between children in intervention and control kindergartens in parental stress and time to initiated locally available supportive action, respectively, will be analyzed in a similar way to the primary outcome.Process measures:◦ Factor structure will be estimated by confirmatory factor analysis (CFA).◦ Agreements between:▪ Reported concern (EWQ) and DBED concluded concern (EWQ), respectively, and mental health (SDQ): correlations (Pearson’s and Spearman), Cohen’s (weighted) Kappa, CFA: uni-, bi-, and tri-factor models representing different sources of information (parent 1, parent 2, teacher. Latent difference score (LDS) models will also be explored for common levels and differences within and between families.Parent’s and teacher’s mental health report (SDQ): correlations (Pearson’s and Spearman), CFA, including method factors, LDS models.Parents’ and teacher’s possible worries for the child: Cross table with chi-quadrat test, Cohen’s weighted Kappa, CFA, and LDS models.▪ Change from reported (EWQ) to concluded concern (EWQ) during the parent-teacher conference: cross table with chi-quadrat test, Cohen’s weighted Kappa, CFA/LDS models.▪ Satisfaction with DBED:Initial: distribution of scores and mean values of each item. Mean value of total score.Follow-up: repeated measures of mean values of each item and total scores and LGC models.▪ Predictors of mental health change, parent concern, teacher concern, parent satisfaction, parental stress: LGC models with predictors (conditional LGC models).Statistical principles◦ Level of statistical significance: We will use the threshold of *p* = 0.05 for the main analysis. However, the threshold perspective has been debated, and there is considerable literature claiming another perspective as a relevant alternative. This implies the use of exact p-values as a degree of certainty of the generalization from sample to population. In the exploratory part of the project, this practice will be used. In addition, we will calculate effect sizes to evaluate the results beyond statistical significance.◦ Adjustment for multiplicity: Detailed power analysis (Monte Carlo analysis) was used to decide sample size for satisfactory power. Adjustment is irrelevant for this analysis. Regarding other statistical analyses, analyses may introduce risk for Type 1 errors when testing family-wise tests. When testing specific hypotheses (see above), no adjustment should be necessary. When exploring differences and relations not pre-specified in hypotheses (family wise tests), Bonferroni corrections will be used.◦ Confidence intervals to be reported: 95%◦ Methods used for assumptions to be checked for statistical methods: Residuals will be saved and checked for normality and homoscedasticity. Relations will be plotted and linearity in relations evaluated.◦ Details of alternative methods to be used if distributional assumptions do not hold: Bootstrapping will be used if normality does not hold. However, larger samples are robust for such deviations.If survival models (Cox and non-proportional parametric hazard models based on Weibull distribution), the proportional assumption will be tested. In addition, covariates will also be tested as time-dependent covariates to explore whether they relate to events differently over time.

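### The chi-square test planned for the paired concern ratings tests association, so its p-value informs neither agreement nor net change

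*Protocol article*

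**What the plan says.** The article's Outcomes {12} section defines two of the process outcomes at issue. The first is "Agreement between parents and teacher in possible concerns for the child measured by percentage of EWQ items rated as the three different response options", the options being "satisfied; a bit uncertain; concerned". The second is "Change from reported to concluded concern during the parent-teacher conference measured similarly as the preceding outcome".

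The process measures in Statistical methods {20a} give the analysis. For parents' and teacher's worries the test is "Cross table with chi-quadrat test", listed with weighted kappa, confirmatory factor analysis (CFA) and LDS models. For change at the conference it is "cross table with chi-quadrat test, Cohen’s weighted Kappa, CFA/LDS models".

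Plans for assessment and collection of outcomes {18a} shows who rates. Each parent and the teacher complete the Early Worry Questionnaire (EWQ) before the conference, and the teacher records the conclusions on it afterwards. Only the intervention group has EWQ data.

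**The concern.** Parent and teacher rate the same child, and so do the reported and concluded scores, on the same three ordered options. The data form a square paired table. The questions are whether the two ratings coincide (agreement) and whether concern moved up or down (change). Pearson's chi-square answers neither. Its null hypothesis is that one rating carries no information about the other, and for two ratings of one child nobody expects that to be true. A small p-value then says only that the ratings are related. A large one does not rule out a shift in the distribution.

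This matters because Step 2 of the method is where parents and teacher compare answers and decide whether there is reason for concern. Whether the conference raises or lowers concern is a natural question of the process evaluation. Section {20a} also says that exact p-values will serve as a degree of certainty in the exploratory part. If the process measures belong to that part, a p-value for the wrong hypothesis would carry weight.

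**Working it through.** The article gives no figure for these analyses, so there is nothing to reproduce. It also gives no EWQ distributions, so **all cell counts below are assumed**. They show what each statistic responds to and do not predict the trial's data.

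**Formulas**

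- Pearson: sum of (O − E)²/E, with E = row total × column total / n; 4 df for a 3×3 table.
- Bowker (symmetry): sum over pairs i<j of (n_ij − n_ji)²/(n_ij + n_ji); 3 df.
- Stuart-Maxwell (equal margins): d′V⁻¹d, with d_i = row total − column total, V_ii = row total + column total − 2n_ii and V_ij = −(n_ij + n_ji), using two of the three categories; 2 df.
- Linear-weighted kappa: 1 − (observed weighted disagreement)/(expected weighted disagreement), with weights |i − j|.

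**Table A: no net change.** Rows 56,12,2 / 12,6,2 / 2,2,6, n = 100. Both margins are 70/20/10.

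- Expected counts: 49,14,7 / 14,4,2 / 7,2,1.
- Pearson = 1 + 0.29 + 3.57 + 0.29 + 1 + 0 + 3.57 + 0 + 25 = 34.7, p = 5e-7.
- The table is symmetric, so Bowker = 0 and Stuart-Maxwell = 0, p = 1.
- Weighted kappa = 1 − 36/60 = 0.40.

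The test is highly significant although upward and downward moves cancel exactly.

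**Table B: clear shift.** Rows 56,63,21 / 16,18,6 / 8,9,3, n = 200. The margins move from 140/40/20 to 80/90/30, that is from 70/20/10% to 40/45/15%.

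- Every cell equals its expected count (for example 140 × 80/200 = 56), so Pearson = 0, p = 1.
- Bowker = 47²/79 + 13²/29 + 3²/15 = 27.96 + 5.83 + 0.60 = 34.4, p = 2e-7.
- Stuart-Maxwell: d = (60, −50), V = [108, −79; −79, 94], determinant 3,911. The statistic is (94 × 3,600 − 2 × 79 × 3,000 + 108 × 2,500)/3,911 = 134,400/3,911 = 34.4, p = 3e-8.
- Weighted kappa = 0, so kappa gives no direction of shift either.

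**Table C: strong disagreement.** Rows 2,3,30 / 3,24,3 / 30,3,2, n = 100.

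- Pearson = 115.0, p = 6e-24.
- Raw agreement = (2 + 24 + 2)/100 = 28%; weighted kappa = 1 − 132/91 = −0.45.
- The table is symmetric, so Bowker and Stuart-Maxwell give p = 1.

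Pearson rejects although the raters systematically disagree. The marginal tests see nothing either, so they cannot stand in for an agreement measure.

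**Alternative layout: rater (or occasion) by response.** Dichotomised pairs 70,12 / 2,16, n = 100, have margins 82/18 and 72/28. An ordinary chi-square on 82,18 / 72,28 treats the two ratings of each child as independent and gives 2.82, p = 0.093. McNemar on the same pairs gives (12 − 2)²/(12 + 2) = 7.14, p = 0.0075. This layout asks about change but discards the pairing.

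**The case against.** The chi-square is not the only method listed. Weighted kappa addresses agreement. LDS models can estimate the size and direction of within-pair change. The outcome definition itself uses the percentages in each response option, so the shift in Table B would be visible whatever the chi-square gives. All of this stands, and it limits the consequence.

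Three further points have weight:

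- The chi-square variant is not named. McNemar, Bowker and Stuart-Maxwell are also chi-square statistics on cross-tables. If one of them is meant, the part on change falls away and naming it settles the matter. The ordinary reading of the wording is still Pearson.
- Table B needs reported and concluded concern to be exactly independent. That is an extreme case, given that the teacher who records the conclusion also rated the child beforehand. It shows what the test can miss, not what is likely.
- A marginal test would not repair the agreement analysis, as Table C shows. For agreement, the useful measure is the kappa already planned.

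A reader might infer more than the document supports: that a large shift at the conference would go unnoticed, or that the authors would read a significant chi-square as change or disagreement. The first is contradicted by the LDS models and the percentages, and the article nowhere states the second. A reader might also suppose that the 37 items are pooled as if independent. The article does not say that the cross-tables pool items, so this is only a condition to guard against.

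**Conclusion.** The point holds as a mismatch between a named test and the question it serves. Read as Pearson's, the chi-square p-value informs neither parent-teacher agreement nor reported-to-concluded change. In the constructed tables it ranges from 5e-7 with no net change to 1 with a clear shift.

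The size is minor. It concerns process outcomes in the intervention arm, with suitable measures planned beside the test. It does not make the process conclusions wrong, because they need not rest on this p-value, and it does not reach the primary or secondary treatment comparisons. The conclusion rests on the ordinary reading of the test's name. The table counts are illustrative, but the point does not depend on any particular set of them.

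**What to change.** - **Reported-to-concluded change, and systematic parent-teacher differences in level:** replace the chi-square with a paired marginal-homogeneity test (Stuart-Maxwell or Bowker), or with an ordinal mixed model that has an effect for rater or occasion and random effects for child and kindergarten. If a paired chi-square was intended, name it.
- **Parent-teacher agreement:** drop the chi-square and report weighted kappa with a 95% confidence interval, the level that {20a} already sets.
- **If items are pooled:** account for items nested in child, or analyse at child level.

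The cost is analysis wording only. Data collection, sample size and the planned kappa and LDS analyses stay as they are.

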### Trial design {8}

The study design is a cluster randomised open trial, where 20 kindergartens will be randomised to either DBED intervention (*n* = 10) or control groups (*n* = 10). In the control group, parent-teacher appraisals are performed in the traditional way (treatment as usual; TAU). Children’s mental health, as measured by SDQ scores, will be assessed by both parent- and teacher-report biannually through the last 3 years in kindergarten and for the first 2 years in school. Our analyses will examine DBED’s possible superiority to TAU. Similar analyses will be performed as to DBED’s impact on activation of interventions for mental health concerns and parental stress.

The number of components involved, the wide variety of behaviours targeted, expertise and skills required by those delivering the intervention, and the permitted level of flexibility of the intervention confirm that the PRO-DIALOG project is complex intervention research [11]. Hence, in addition to the core trial design, we will use a mixed-method approach to the process evaluation, including both quantitative and qualitative methods. A logic model of the project can be found in Additional file 1.

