### Outcomes {12}

Primary outcome:

Effect of DBED on mental health measured as the difference between intervention group and control group in Total difficulties score of SDQ. Measurement scores will be recorded every sixth month during the entire 5-year project period (i.e., child-age 3 to 8 years) as repeated measures. SDQ sub-scores and two impact scores (difficulties in general and impact on four areas of daily functioning) will be analyzed. The primary endpoint will be during the last 3 months in kindergarten before the child starts school, giving total change over six time points of measurements. The secondary endpoint will be during the last 3 months in the second school year (10 time points of measurements).

Secondary outcomes:

Effect of DBED on time to initiated locally available supportive action analyzed as the difference in time (months) from inclusion to activation of such actions between the intervention group and control group as mean time (months) from inclusion to activation of such actions. This outcome will indicate if DBED may lead to earlier supportive actions for children.Effect of DBED on parental stress analyzed as the difference in total scores of the PSS between the intervention group and the control group [12]. Measurements will be recorded every sixth month during the project period. This outcome will indicate if DBED may lead to less or more parental stress and more or less self-confident parents.

Process outcomes:

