### Sample size {14}

The participating children are expected to represent the general population and are not a clinical sample with a presumed high level of mental symptoms. Hence, even if DBED will have a promoting effect on mental health among the children, the difference between the intervention and the control group will probably be small. In the absence of other similar studies, we chose a difference of 0.8 in SDQ Total Difficulties Scale score based on discussions in the project group. Then, we powered the study to be able to detect such a difference between the implementation and the control group. Mplus was used for Monte Carlo simulations assuming the participation of 20 kindergarten (clusters) with ten participating subjects within each cluster and a baseline SDQ mean 5.5 (English norm data: 5.7) SD = 5.5 (σ^2^_within_ = 30.25). The group differences were represented with a predictor of the slope factor in a latent growth curve model. The model assumed normative stability in the controls (mean change = 0.0) and a reduction of −0.8 in the intervention group during the total period. Group sizes were set to be equal. Some between-cluster variation was specified in the intercept factor (σ^2^_between_ = 2.0) to give expected ICC = 0.10 in the six outcome variables over time. The attrition was assumed to be up to 25%. The number of replications was 1000. To achieve the difference of 0.8 with a sample size of *n* = 100 in each group, the statistical power for the testing of group difference was found to be 95%.

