## Assignment of interventions: allocation

### Sequence generation {16a}

To prevent contamination from intervention to control cases, the separate kindergartens will be assigned to either intervention or control condition. Because the kindergartens will be recruited from three different organisations, randomizing will be performed within each organisation (block randomisation). The randomisation will be computer-generated by a staff member at Research Unit for Health Surveys, University of Bergen, who is not a part of the PRO-DIALOG project.

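### The model for time to supportive action is not fixed, and the survival models mentioned conditionally carry no kindergarten term although kindergartens were randomised

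*Protocol article*

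**What the plan says.** **Randomised unit.** Trial design {8}: "20 kindergartens will be randomised to either DBED intervention (*n* = 10) or control groups (*n* = 10". Sequence generation {16a} confirms that "the separate kindergartens will be assigned to either intervention or control condition", with randomisation done separately within each of the three owner organisations.

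**Outcome.** Outcomes {12} lists as a secondary outcome "Effect of DBED on time to initiated locally available supportive action". It describes the contrast as a difference between arms in mean months from inclusion to the start of an action. The participant timeline shows actions recorded at the six kindergarten assessments.

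**Analysis.** Section {20a} says two things that bear on this outcome:
- It is to be handled much like the primary outcome, that is, by latent growth curve models, which the protocol equates with linear mixed or multilevel models.
- Later, under statistical principles: "If survival models (Cox and non-proportional parametric hazard models based on Weibull distribution), the proportional assumption will be tested". Time-dependent covariates will also be explored. The sentence names no outcome and no clustering term.

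**Clustering elsewhere.** Sample size {14} was simulated "assuming the participation of 20 kindergarten (clusters) with ten participating subjects within each cluster", and "Some between-cluster variation was specified in the intercept factor" "to give expected ICC = 0.10 in the six outcome variables over time". These inputs are for the SDQ. The Discussion says that differences between the groups will be adjusted for with a multi-variable and multi-level approach.

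**The concern.** The text gives two routes to an analysis of this outcome, and neither is complete.

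The growth-curve route needs repeated scores from each child. Time to first supportive action is one value per child, and it is censored for any child who has no action by the last recording. There is no trajectory to fit, and a mean time is not defined for the censored children without further assumptions.

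The survival route suits the data. Among the quantitative outcomes listed, this is the only one that the Cox and Weibull remark could serve. But the remark lists what will be tested and explored without mentioning the unit that was randomised. A standard Cox or Weibull model would treat about 200 children as independent.

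Supportive actions are agreed at the conference between parents and kindergarten staff, and some are simple educational measures within the kindergarten. How readily support starts may therefore be partly a property of the kindergarten. If that variation is left out of the standard error, the interval for the arm effect is too narrow. A chance difference among a few kindergartens could then be reported as DBED bringing support forward.

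**Working it through.** **Plan's own figure.** There is none to reproduce. The protocol gives no power, event count, ICC or false-positive rate for this outcome; its 95% power refers to the SDQ.

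**Inputs**
- Clusters: 20 kindergartens, 10 per arm (Trial design {8}).
- Children per kindergarten: m = 10 (Sample size {14}).
- Nominal level: 0.05 (section {20a}: "We will use the threshold of *p* = 0.05 for the main analysis"). Two-sided testing is assumed, as is applying this level to the secondary outcome.
- ICC: unknown for this outcome, so a range is shown. Two values come from the SDQ inputs in Sample size {14}: the stated 0.10, and the value implied by the stated variances, 2.0 / (2.0 + 30.25) = 0.062. The two differ, and the section does not show how 0.10 was reached.

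**Formula.** With equal cluster sizes and the arm constant within a kindergarten, a test that ignores kindergarten understates the variance of the arm contrast by about

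DE = 1 + (m − 1) × ICC

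and its actual two-sided false-positive rate is about

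2 × [1 − Φ(1.96 / √DE)].

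| ICC | DE (m = 10) | False-positive rate |
|---|---|---|
| 0.01 | 1 + 9 × 0.01 = 1.09 | 6.1% |
| 0.02 | 1 + 9 × 0.02 = 1.18 | 7.1% |
| 0.05 | 1 + 9 × 0.05 = 1.45 | 10.4% |
| 0.062 | 1 + 9 × 0.062 = 1.558 | 11.6% |
| 0.10 | 1 + 9 × 0.10 = 1.90 | 15.5% |

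For example, at ICC 0.10: 1.96 / √1.90 = 1.42, and 2 × [1 − Φ(1.42)] is about 15.5%.

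**Sensitivity to cluster size at ICC 0.10**
- m = 7.5 (10 less 25% attrition): DE = 1.65, rate 12.7%.
- m = 11: DE = 2.0, rate 16.6%.
- m = 12: DE = 2.1, rate 17.6%.

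The Discussion expects more than 100 + 100 participants, so with 20 kindergartens the clusters may exceed 10.

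**Simulation check with censored times.** The settings were 20 kindergartens of 10 children, no treatment effect, kindergarten event probabilities drawn from a beta distribution, 25% of children exposed to early censoring, six half-yearly intervals, and 3,000 runs per setting. Assumed three-year event probabilities were 10%, 20%, 30% and 50%. Ranges are over these event probabilities.

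| ICC | Log-rank (Cox score) test ignoring kindergarten |
|---|---|
| 0 | 5.0-5.4% |
| 0.02 | 5.8-7.1% |
| 0.05 | 9.6-11.2% |
| 0.062 | 9.0-12.6% |
| 0.10 | 14.6-15.8% |

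The simulation agrees with the formula. In the same runs, a t-test on the 20 kindergarten event rates (18 degrees of freedom) had a false-positive rate of 3.5-5.8%.

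**Effect on the interval.** A correct interval is wider by a factor of about √DE: √1.18 = 1.09 at ICC 0.02, √1.45 = 1.20 at 0.05 and √1.90 = 1.38 at 0.10.

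**The case against.** The strongest reply is that the protocol never plans an unclustered survival analysis. The survival sentence is conditional, concerns assumption checks, and specifies no complete model. The outcome is formally referred to the primary approach, which the protocol equates with multilevel models. Only the slope is described there as varying between individuals; the level of the random intercept is left open, and the sample size model puts kindergarten variance in the intercept. The mention of within-level residual structures fits a two-level model. The Discussion's multi-level remark is not limited to one outcome. Finally, the exact form of cluster adjustment is detail that a condensed article may leave to the full protocol or analysis plan.

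Much of this stands. A reader might infer that Cox and Weibull models are prescribed for this outcome and that clustering will be ignored; the text supports neither. A reader might also infer a fixed false-positive rate of 10-17%. That is not supported either: it carries an SDQ-type ICC over to a different kind of outcome, leaves out small ICCs, and by the formula reaches 17% only with about 11-12 children per kindergarten at ICC 0.10. Nor does the text expressly tie the 0.05 threshold to secondary outcomes, although it says that specific hypotheses need no multiplicity adjustment.

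What the reply does not settle is which model is meant. The growth-curve reference cannot serve a single censored time, so whatever kindergarten level it may imply does not carry over by itself to a survival model. The Discussion's remark concerns imbalance between the groups, not the standard error of this comparison. Section {20a} goes into assumption tests and time-dependent covariates but never names kindergarten.

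**Conclusion.** The point holds in a limited, conditional form. Section {20a} does not fix how time to supportive action is analysed: one route does not suit the outcome, and the other is mentioned conditionally and without the randomised unit. This is an ambiguity in the plan, not a stated intention to ignore clustering.

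If a survival model were run without kindergarten, the false-positive rate with 10 children per kindergarten would be about 6-7% at ICC 0.01-0.02, about 10% at 0.05, about 12% at 0.062 and about 15-16% at 0.10, instead of 5%. These figures assume 20 roughly equal clusters, two-sided testing, and an ICC that the protocol does not give for this outcome. The true ICC could be lower or higher than the SDQ values. The primary SDQ analysis is not affected by this point.

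**What to change.** In section {20a}, replace the reference to the primary approach, for this outcome only, with a named survival model that carries the design. For example:

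*Time to first supportive action will be analysed with a Cox model (or a Weibull model if proportional hazards fails), with children who have no action censored at their last recording. The model will account for kindergarten by a shared frailty, or by kindergarten-clustered standard errors with a small-sample correction for 20 clusters, and for the owner organisation within which kindergartens were randomised.*

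One of the two kindergarten options should be chosen in advance. Because 20 clusters are few, a permutation test that reassigns kindergartens within owner organisation would be a useful but optional check.

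The change takes a sentence or two, standard software and no new data. The price is a wider confidence interval and less apparent power for this secondary outcome.
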